### Population and Sample Size

Schools will be invited to participate either as intervention or control school. In the attempt to be most inclusive, all children of grades 2 and 3 of the participating schools are allowed to take part. In intervention schools, all children will be taught with PAAC, though only children whose parents/legal representatives gave written informed consent will be included in the measurements of physical fitness, health parameters, cognitive/mental and social abilities. Children of both sexes, different socio-economic backgrounds and cultural contexts, and from urban as well rural areas will be enrolled. No child will a priori be excluded, neither from physically active learning nor from the measurements performed. However, any pre-existing disability or illness will be recorded and considered when validating the results for the children. Furthermore, each child may deny participation at any time in the course of the study or for a certain measurement.

In each country, aged-matched children of a different school will be included as the control group. Healthy children of both sexes, aged 7–9 years (in grade 2–3), will be tested at the same time intervals as children from the intervention schools. Children in the control group will not receive active learning throughout the duration of the project, but will be taught according to the usual didactics.

Assuming that the prevalence of NCDs varies across schools, following a normal distribution with a mean value of 3% and a SD of 2%, a prevalence rate of about 5% would be expected. The power calculation for the intervention study is based on the change in a quantitative outcome variable from baseline to follow-up. Annually analyses between intervention and control schools in numerous variables, the sample size for a parallel group design is calculated using *n* = 2 · (σ / Δ) 2 · k, where n represents the number of participants in each group, σ (sigma) the expected standard deviation of the observations (which is assumed to be equal for all groups), Δ (delta) gives the relevant difference between observations, and k is the constant in this study, chosen based on the common values by a double-sided *t*-test set at 5% and with test strength 80% (this corresponds to a *k* of 7.9). Based on these calculations we have determined the sample size to be adequate for all variables for all ages, also when divided by sex (Table 1).

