**Table 1 T1:** Based on the various tests, the following sample sizes for each group (intervention and control schools) were calculated as adequate for analyses, with a power of 80% and alpha of 5%.

	**Variables**	**Methods**	**Number of children in each group/total**
Anthropometry	Weight, height, IsoBMI, fat-, fat-free and muscle-mass, WHtR	Measuring tape, body composition analyzer	34^*^/68 and 64^**^/128
Physical activity level	MVPA 60 min/day, VPA (min/day) and inactivity (min/day)	24-h activity monitor (Actigraph) for 1 week	126^***^/252
General physical capacity (fitness)	Strength test (kg) and Andersen Running Test	Jamar Handgrip	73^*^/146
Blood values	HDL and total cholesterol, Glycated hemoglobin (HbA1c), hemoglobin, hematocrit, ferritin, iron, and red blood cell (RBC) count	Blood analysis	126^***^/252
Quality of Life and SDQ?	LQ_0−28_	ILC questionnaire, parental and child response	34^*^/68
Diet	Intake of fat, sugar, fruit/vegetables and confectionary in diet	Questionnaire	73^*^/146
Cognitive ability	Executive functions	Eriksen flanker test Stroop test	24^*^/48
Behavioral screening	Mapping of emotions, body image and friendship	BUS-Test	85^*^/170
Academic performance	Score in national test for English, Mathematics and native language	Local and national academic tests	34^*^/68

*Statistical program: Systat 13, Power analyses*.

* *one-sample t-test*,

** *two-sample t-test*,

*** *Z-score*.

In the present study we will recruit ~3,000 + pupils in three countries. As can be seen in Table 2, the number of pupils recruited are sufficient for analyzing the questions established in Table 1.

**Table 2 T2:** Estimated sample size for HAPHC.

	**Intervention schools**	**Control schools**	**Total**
Austria	558	198	756
Slovenia	936	225	1,161
Belgium	798	398	1,196
Total *n* of children	2,292	821	3,113

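### The blanket claim of adequate sample size ignores clustering by school; whether 80% power holds depends on an ICC and effect sizes that the protocol does not give

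*Protocol article*

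**What the plan says.** Under Population and Sample Size, schools are invited as either intervention or control schools, and each country's control children come from a different school. The size is computed as n = 2·(σ/Δ)²·k with k = 7.9, for a two-sided 5% test and 80% power, "where n represents the number of participants in each group". σ is "the expected standard deviation of the observations (which is assumed to be equal for all groups") and Δ "gives the relevant difference between observations"; neither has a value for any outcome.

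Table 1 lists 24 to 126 children per group, with footnotes naming a one-sample t-test, a two-sample t-test or a Z-score. Table 2 expects 2,292 intervention and 821 control children, 3,113 in total. From this the article concludes "Based on these calculations we have determined the sample size to be adequate for all variables for all ages, also when divided by sex", and before Table 2 it adds that "the number of pupils recruited are sufficient for analyzing the questions established in Table 1".

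The Abstract speaks of 12 schools. Possible Limitations lists three confirmed schools in each of three countries, so nine. The Statistical Protocol names dependent t-tests, repeated measures ANOVA and ANCOVA, with no school term.

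**The concern.** Children in one school share teachers, neighbourhood and curriculum, and here they also share the intervention status. Precision therefore depends on the number of schools, above all control schools, as well as on the number of children. Comparing 3,113 children with Table 1 settles adequacy only if children within a school are independent.

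Two errors of interpretation are at stake. A null result, especially within a sex or grade, could be taken as evidence of no effect from a study declared adequately powered. And if children are analysed as independent, differences between schools could be reported as effects of the intervention.

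**Working it through.** **The plan's own constant.** (1.960 + 0.842)² = 7.85, which agrees with 7.9. The constant is right; the issue is what the formula leaves out.

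**Effect sizes behind Table 1.** With no σ or Δ given, they can only be back-solved. For n = 126 (activity, blood values):
- by the stated formula, d = √(2 × 7.9/126) = 0.354;
- if a one-sample z-test was used, d = √(7.9/126) = 0.25.

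The footnote for these rows says only Z-score, so both are carried forward.

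**Assumptions.** ICC of 0.01 to 0.05 for the outcome analysed; 12 schools split 9/3; equal school sizes within each arm; sexes and grades of equal size and present in every school.

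**Formulas.** School size m is 2,292/9 = 254.7 (intervention) and 821/3 = 273.7 (control). Design effect per arm: DE = 1 + (m − 1)·ICC. SE in SD units: √(DE_i/n_i + DE_c/n_c). Power comes from a noncentral t with noncentrality d/SE and 12 − 2 = 10 df. For one sex, n and m are halved; for one sex in one grade, quartered.

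**Pooled precision.**

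| ICC | DE interv./control | Effective children | SE |
|---|---|---|---|
| 0.01 | 3.54 / 3.73 | 648 / 220 | 0.078 |
| 0.02 | 6.07 / 6.45 | 377 / 127 | 0.103 |
| 0.05 | 13.68 / 14.63 | 168 / 56 | 0.154 |

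**Power: pooled / by sex / by sex and grade.**

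| d | ICC 0.02 | ICC 0.05 |
|---|---|---|
| 0.354 | 87 / 82 / 73% | 54 / 52 / 47% |
| 0.25 | 60 / 54 / 45% | 31 / 30 / 27% |

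For d = 0.5 the pooled comparison has 99% power at ICC 0.02 and 83% at 0.05; it reaches 80% at about 0.055. For d = 0.25 the pooled break-even ICC is about 0.011. At ICC 0.05 the smallest effect detectable with 80% power is about 0.48 SD.

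**Sensitivity to the schools.** With 12 schools split 6/6, the pooled break-even ICC is 0.073 for d = 0.5 and 0.0145 for d = 0.25. With nine schools split 6/3 (7 df) it is 0.044 and 0.008, and power for d = 0.25 is 75% at ICC 0.01 and 52% at 0.02.

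**Type I error if schools are ignored.** The SE for independent children is √(1/2,292 + 1/821) = 0.0407. The true size of a nominal 5% test is 2·[1 − Φ(1.96 × 0.0407/SE)]. At ICC 0.01, 1.96 × 0.0407/0.0780 = 1.02, which gives about 0.31. At ICC 0.02, 1.96 × 0.0407/0.1025 = 0.78, which gives about 0.44.

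**The case against.** A reader might infer that the stated 80% power is simply not delivered. The documents do not support that. Planned enrolment far exceeds Table 1 (821/64 = 12.8 times the two-sample row in the smaller arm), and this absorbs a substantial design effect: medium effects stay well powered in the pooled comparison unless the ICC passes about 0.055.

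A reader might also take the ICC from the article's remark, "Assuming that the prevalence of NCDs varies across schools, following a normal distribution with a mean value of 3% and a SD of 2" per cent. At face value that gives 0.02²/(0.03 × 0.97) = 0.0004/0.0291 = 0.014. But it describes a binary prevalence, whereas the next sentence bases power on change in a quantitative outcome, so it is not the protocol's ICC for these variables. Even if it were used, d = 0.354 with a 9/3 split would have 95% power pooled, 91% by sex and 81% by sex and grade. The 126 rows would then pass under the article's own formula. The smaller d = 0.25 is one reading of a footnote, and no passage states the 9/3 split. These objections stand, and they rule out a flat statement that the trial is underpowered.

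They do not rescue the claim itself. It covers all variables, all ages and both sexes, and it was derived without the quantity on which it depends. Nor is this detail left to a fuller document: the article prints the formula, the resulting numbers and the conclusion. A separate analysis plan could still add a school term, so the type I error figures hold only if the named tests are applied to children as independent units.

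**Conclusion.** The concern holds in this form: the universal adequacy claim is unsupported because the calculation does not fit a design in which schools are the assigned units. Whether 80% power remains depends on an ICC and effect sizes that are not stated. Under the assumed 9/3 split, power is safe for d = 0.5 pooled at an ICC up to about 0.055. At d = 0.354 it is lost within sex-by-grade groups by ICC 0.02 and in every comparison by 0.05. At d = 0.25 it is lost even in the pooled comparison just above ICC 0.01. With only the nine confirmed schools (6/3) these limits are tighter; with a 6/6 split of 12 they are looser. If children are analysed as independent, false positives are the larger risk: about 31% at ICC 0.01 and 44% at ICC 0.02, against a nominal 5%.

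**What to change.** - Recalculate Table 1 with 1 + (m − 1)·ICC over a stated range labelled as assumed (for example 0.01 to 0.05), with degrees of freedom based on schools.
- State the effect size and the test behind each Table 1 row.
- Reconcile the 12 schools of the Abstract with the nine in Possible Limitations, and state the intervention/control split.
- Give the difference detectable with 80% power for those schools, pooled and by subgroup.
- Replace the statement that the sample is adequate for all variables, ages and both sexes, and its repetition before Table 2, with that result. Label sex and grade subgroup analyses exploratory.

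The cost is a recalculation and a less favourable power statement. Enrolment does not need to change.

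### Seven of the ten per-group sizes in Table 1 are one-sample sizes: they omit the factor 2 of the protocol's own formula and give about 51–53% power, not 80%, for intervention versus control

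*Protocol article*

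**What the plan says.** All references are to the protocol article.

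- **Population and Sample Size, text.** It states that "the sample size for a parallel group design is calculated using" n = 2(σ/Δ)²k, "where n represents the number of participants in each group". The constant k is "chosen based on the common values by a double-sided" t-test "set at 5% and with test strength 80" per cent, which the text equates with 7.9. σ is "the expected standard deviation of the observations (which is assumed to be equal for all groups"; Δ "delta) gives the relevant difference between observations". No value of σ or Δ is given for any variable. The text then concludes that the sample is adequate for every variable and age, and also within each sex, and points to Table 1.
- **Table 1, caption.** "sample sizes for each group (intervention and control schools) were calculated as adequate for analyses, with a power of 80" per cent and an alpha of 5%. Each entry is also doubled to give a two-group total (34/68, 73/146 and so on).
- **Table 1, footnotes.** Seven of the ten sizes carry the single asterisk, "one-sample t-test": anthropometry 34, fitness 73, quality of life 34, diet 73, cognitive ability 24, behavioural screening 85, academic performance 34. One size (anthropometry, 64) is marked as two-sample. Two sizes (126, for activity level and blood values) are marked only as Z-score.
- **Statistical Protocol.** The main analysis compares the change from baseline in intervention-school children with that in control-school children. Dependent t-tests, repeated-measures ANOVA and ANCOVA are the named methods.
- **Table 2.** It gives 2,292 intervention and 821 control children, and the article calls these numbers sufficient by reference to Table 1.

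**The concern.** The formula, the caption and the stated main analysis all concern a comparison of two groups. A one-sample test compares one group with a fixed value, or tests change within one group. It carries no sampling error from a second group, so it needs about half as many children per group for the same standardised effect. If a one-sample size is printed as the size needed in each of two groups, the stated 80% power is wrong.

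Table 1 is the yardstick against which the article calls its sample adequate. Anyone who uses it to decide whether a smaller cell (one sex, one grade, one country) can support a comparison would be working with thresholds about half of what the article's own formula requires.

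**Working it through.** **Inputs.** Two-sided alpha 0.05, power 0.80, k = 7.9 and the two-group formula are from Population and Sample Size; the printed sizes and their test labels are from Table 1; the enrolment figures are from Table 2. σ and Δ are not stated, so the standardised effect d = Δ/σ is backed out from each printed size. That is an assumption.

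**1. The constant.** (1.960 + 0.842)² = 7.85, which rounds to the stated 7.9.

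**2. Reproducing the printed figures.** The anthropometry row gives both a one-sample and a two-sample size. With exact noncentral-t power at d = 0.5:
- one-sample t-test: 33.4, so 34;
- two-sample t-test: 63.8, so 64 per group (the article's formula: 2 × 7.9/0.25 = 63.2).

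Both printed figures are recovered at a single effect size. As a two-sample size at d = 0.5, 34 cannot be recovered: the two-sided t-test needs 64, the normal approximation 63 and a one-sided t-test 51. The other single-asterisk sizes agree with their label: 24 at d = 0.6 (23.8), 73 at d = 1/3 (72.6), 85 at d ≈ 0.307.

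**3. Correcting the seven sizes.** For each printed n, d is the effect that a one-sample t-test detects with 80% power. That d is then put into the article's formula, 2 × 7.9/d², and into the exact two-sample t-test.

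| Printed n | Implied d | Formula, per group | Exact t, per group | Two-group power at printed n |
|---|---|---|---|---|
| 24 | 0.597 | 44.3 | 45.0 | 52.6% |
| 34 | 0.495 | 64.5 | 65.0 | 52.1% |
| 73 | 0.332 | 143.0 | 143.1 | 51.4% |
| 85 | 0.307 | 167.2 | 167.1 | 51.3% |

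At d = 0.5 exactly, 34 per group gives 52.9% and the requirement is 64. To keep 80% power with 34 per group, d would have to be about 0.69.

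**4. Why the power loss hardly depends on Δ.** Halving the required n divides the expected test statistic by √2: Φ(2.802/√2 − 1.960) = Φ(0.021) ≈ 0.51. The exact t-test adds a point or two for small n.

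**5. The 126 entries.** A one-sample z-test gives 7.85/0.25² = 125.6, so 126, at d = 0.25. A two-sample z-test gives 126 per group at d = √(2 × 7.85/126) ≈ 0.353. The Z-score label does not say which was used.

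**6. What this does to the planned sample** (no clustering).
- *Pooled.* 821 controls and 2,292 intervention children exceed every corrected size. With equal splits, one sex has about 821/2 ≈ 410 controls, and one sex in one grade about 821/4 ≈ 205. Both still exceed 167.
- *A cell that the printed size would pass wrongly.* Austria, one sex, equal split: 198/2 = 99 controls and 558/2 = 279 intervention children. The 99 exceeds the printed 85. At d = 0.307 the expected statistic is 0.307 × √(99 × 279/378) ≈ 2.63, and the exact t-test has about 75% power.

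**The case against.** **A within-group reading.** The article bases power on change from baseline and names dependent t-tests. A one-sample test on change scores is the right size for change within each group, so the numbers could be correct for an analysis that the article names, with only the caption at fault. This is the best defence. It justifies keeping the one-sample sizes under a proper label. It does not reconcile them with a parallel-group formula, a caption about intervention and control schools, and a main analysis of the difference in change between them.

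**Smaller variance of change scores.** A baseline correlation of about 0.73 would also reduce 64 to 34. The article does not say this, and its footnote gives a different reason for the 34.

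**Back-solved effects.** Any n matches some d, so matching 73 or 85 proves little by itself. That is fair: the evidence is the footnote label and the 34/64 pair, and the other matches only agree with it.

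**Stronger readings that the article does not support.** A reader might count the 126 entries as one-sample too, correct them to about 253, and note that the Austrian control arm (198), the Slovenian control arm (225) and a pooled sex-by-grade control cell (about 205) lie below that. The first step is inference from an ambiguous label. The second ignores the allocation: 253 applies to equal groups, whereas Table 2 has many more intervention than control children. At d = 0.25 without clustering, power is 85.5% for Austria (558 v 198), 92.0% for Slovenia (936 v 225) and 86.6% for the pooled cell (about 573 v 205). None of these falls short.

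**Conclusion.** The point holds for the seven single-asterisk sizes. As per-group sizes for intervention versus control they are about half of what the article's formula requires, and the stated 80% is in fact about 51–53%. That power figure barely depends on the unstated σ and Δ. The corrected sizes do depend on the effects implied by the printed numbers.

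A reader might infer that the trial itself has 52% power. It does not follow: that figure belongs to a hypothetical comparison with exactly 24, 34, 73 or 85 children per arm. Nor does the article's statement about ages and sexes fail for these seven sizes when countries are pooled, on equal splits and before clustering. What fails is the table as a yardstick for smaller cells, such as one sex within one country. The Austrian example assumes an equal sex split and no clustering. The 64 stands, and nothing can be concluded about the 126 entries until their basis is stated.

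**What to change.** 1. Recompute the seven single-asterisk sizes with the two-group formula under Population and Sample Size, and state σ and Δ for each variable.
2. Keep a one-sample size only if it is relabelled as the size for within-group change, beside the two-group size. Leave the 64 as it is.
3. State which test, σ and Δ lie behind the two 126 entries, and correct them only if they prove to be one-sample.
4. Restate, with the unequal allocation of Table 2, which pooled, sex, grade and country comparisons reach 80% power, and rest the sufficiency statement on that.

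The cost is a recalculation and corrected table text. Some subgroup statements will become less favourable. No extra children are needed.

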**Methods:**

In three European countries (Austria, Slovenia, and Belgium), 12 primary schools in total will be recruited to act as either intervention or control school in a large intervention study, which applies the PAAC pedagogy during lectures. It is estimated that, at least 3,000+ children across the three countries will be recruited in this study. All teachers of intervention schools will receive training and materials/teaching equipment that will allow them to integrate a daily PA unit of 45 min over 3 years across the curriculum. In response to the daily PA intervention, the following primary outcomes will be assessed: changes in health related physiological factors, academic achievement, psycho-social aspects and wellbeing.

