About one third of a child's life is spent at school, and about 8–10 h 5 days a week this time is spent mainly sedentary attending lessons (3, 25, 26) with a strong trend toward decreasing PA with increasing age. Furthermore, many children lack the possibility and/or stimulation to PA at home (15, 27). Therefore, the school not only has a major responsibility to stimulate and promote healthy living in children, but also opens a wide time window to continuously and consequently integrate PA into children's everyday life (28). Several school-based PA interventions have been sucseccfully implemented in school-children of different age (17, 29–37). Results of the MOVI-Kids study for example indicated increased cardiorespiratory fitness and muscular strength and velocity after implementation of three 60 min PA sessions per week in 4–7 year old children after only a couple of months (36), and the Sogndal school-intervention study showed a reduction in a cardiovascular risk cluster score with a 60 min teacher controlled daily PA in elementary school children after 2 years (31, 35). Aside projects at site, several “online” intervention programs—providing materials, information and evaluation—similarly indicate increased PA and sustained improvement of cardiorespiratory fitness (37–39) and students' physical self-worth (32, 34, 40), and represent an alternative approach in unfavorable times such as pandemic related school lock-downs (41). One of those international programs is the KaziBantu project of the UNESCO Chair on Physical Activity and Health in Educational Settings, a school-based intervention program, aiming to improve physical education and healthy active living of school children and teachers in low-resource settings in South Africa (42, 43). Although “online” programs are well-received and offer a the possibility to implement PA at large scale and to low cost, continued project monitoring is needed to warrant the quality of implementation (38, 44, 45).

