## Aims and Objectives

The overall aim of the longitudinal controlled HAPHC-study is to enhance health and academic performance by use of PAAC and therewith support children's quality of life and wellbeing. By application of the same well-established methods and materials in three European countries, evaluation of effects is performable at large-scale, a question that was left largely unexplored in many previously reported studies (29). Based on the findings of the HAPHC project, key health risk factors should be identified and practical knowledge for the implementation is expected, to provide adaptation for the transfer to all European countries in near future.

Specific research questions of the HAPHC project are with regard to efficiency:

1 Physical activity and health related outcomes: How/does a daily unit of MVPA integrated into learning change physical fitness, PA during leisure time and cardio-metabolic health of elementary school children?2 Academic achievement: How/does a PAAC pedagogy change academic achievement, in particular with regard to main topics (maths, language) and executive function?3 Mental health and quality of life: How/does a daily unit of MVPA integrated into learning change a child's mental state (anxiety, depression), quality of life and well being?

Secondary research objectives of the HAPHC project are with regard to pedagogy, feasabiliy and dissemination:

1 Development and adaptation of teaching equipment/material for PAAC in elementary schools.2 Dissemination of knowledge and large-scale pan-European transfer.3 Integration into the elementary school's curriculum and into teacher's training/education at university level.4 Promotion of public health and prevention of NCDs.

This research further aims at promoting public health within increased PA, healthy diet and prevention of NCD's among children throughout elementary schools. The focus is on the following thematic areas: (i) learning and cognition, (ii) nutrition and growth, including obesity, (iii) PA and health, (iv) mental health and quality of life. Children of both sexes will perform similar PAAC learning throughout the project. This will empower all girls and boys from different socioeconomic, cultural and health status settings and contexts to perform PA while learning.

The specific objectives of HAPHC are:

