### Statistical Protocol

All children will be measured regarding the variables of interest (Table 1) before the implementation of PAAC starts at each intervention school as well as in the control schools (baseline). At the end of the first school year with PAAC in intervention schools, all children will be measured/tested again (1st follow-up). The same measurements/tests will be performed after the 2nd and 3rd year of implementation in all schools.

All data collected will be explored with regard to their distribution and potential outliers before being further analyzed. Main focus of the analyses will be the evaluation of changes in parameters of interest (physical fitness, anthropometry, quality of life, cognition etc.) from baseline to follow-up(s), depending on the intervention. Thus, comparing if the magnitude of change differs between children from intervention schools compared to children of the control schools. Depending on the number of variables and time-points to be compared in one analysis, dependent *t*-tests, repeated measures ANOVA and/or ANCOVA will be performed. Accordingly, a higher increase of, e.g., physical fitness in children of the intervention schools compared to children of a control school is expected.

In case of violations against the assumptions of parametric tests, either data transformations or application of non-parametric tests will be performed.

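### Table 1 lists only per-day activity totals, which in a PAAC school week include the PAAC unit, so they do not by themselves answer the leisure-time part of research question 1

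*Protocol article*

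**What the plan says.** In Aims and Objectives, the first research question is "How/does a daily unit of MVPA integrated into learning change physical fitness, PA during leisure time and cardio-metabolic health of elementary school children". Leisure-time activity is thus a named part of the question.

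Table 1, under Population and Sample Size, gives the physical activity variables as "MVPA 60 min/day, VPA (min/day) and inactivity (min/day"), measured by "24-h activity monitor (Actigraph) for 1 week". The Statistical Protocol section points back to Table 1 for the variables of interest and compares their change from baseline between intervention and control schools. The article defines no leisure-time, out-of-school or weekend activity variable.

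On the intervention, the Abstract says that teachers will "integrate a daily PA unit of 45 min over 3 years across the curriculum". Baseline precedes PAAC, and "At the end of the first school year with PAAC in intervention schools, all children will be measured/tested again (1st follow-up"), with further rounds after the second and third years. On the comparison, "Children in the control group will not receive active learning throughout the duration of the project".

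**The concern.** The question is about activity outside lessons; the listed variables count activity over the whole day. The intervention is itself physical activity, delivered in only one arm, and the monitor records it along with everything else. The difference in change between arms is then the sum of two things: the extra activity delivered in lessons, and any response outside school. A daily total cannot separate them.

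At stake is the interpretation of one named part of research question 1. A child who is more active in lessons and less active at home could show a net gain in the listed variable. If that gain were taken as the answer on leisure time, it would point the wrong way.

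**Working it through.** **Inputs from the article.** Unit length: 45 min daily (Abstract, Methods). School days per week: 5 (Background, where "about 8–10 h 5 days a week this time is spent mainly sedentary attending lessons"). Test: two-sided 5%, power 80%, k = 7.9, with n = 2(σ/Δ)²k per group (Population and Sample Size). Children per group for activity: 126, footnoted as Z-score (Table 1).

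**Assumptions.** The article gives no SD or relevant difference for the activity variables. I take an SD of 15 to 30 min/day, a monitored week with five delivered units, and a share s of the unit that is extra MVPA compared with the same time in control lessons (1, 0.5 or 0.25).

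**Step 1: the plan's own figures.** k = (1.960 + 0.842)² = 7.85, which agrees with 7.9 to rounding. The 126 cannot be reproduced without σ and Δ; it can only be solved backwards. The stated two-group formula gives Δ/σ = √(2 × 7.9 / 126) = 0.354. A one-sample Z formula gives √(7.9 / 126) = 0.25.

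**Step 2: what the unit adds to the weekly average.** Added minutes = 45 × 5 / 7 × s = 32.1 × s min/day.

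**Step 3: what the listed variable would show.** Let L be the intervention-minus-control change in leisure-time MVPA, as a seven-day average. The observed difference is 32.1 × s + L.

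| Share s | Added (min/day) | Observed if L = 0 | Observed if L = −10 | Leisure fall that cancels it |
|---|---|---|---|---|
| 1 | 32.1 | +32.1 | +22.1 | 32.1 |
| 0.5 | 16.1 | +16.1 | +6.1 | 16.1 |
| 0.25 | 8.0 | +8.0 | −2.0 | 8.0 |

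With an illustrative leisure-time fall of 10 min/day, the listed variable has the opposite sign in two of the three cases.

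**Step 4: would such a difference be detected with L = 0?** Power is for 126 per group with a two-sided 5% test, treating children as independent as the plan's formula does.

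| Share s | Standardised difference (SD 30 to 15) | Power |
|---|---|---|
| 1 | 1.07 to 2.14 | about 1.00 |
| 0.5 | 0.54 to 1.07 | 0.989 or more |
| 0.25 | 0.27 to 0.54 | 0.566 to 0.989 |

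At half share or more, the difference exceeds the 0.354 SD implied by 126 per group, with no change in leisure time at all. At a quarter share it may or may not be detected.

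**The case against.** Two stronger readings are tempting. A reader might infer that the monitor data cannot answer the leisure-time question. They can: a 24-hour, one-week record covers after-school hours and weekend days, so the limitation lies in the listed variable and not in the measurement. A reader might also infer that whole-day activity must rise in the intervention arm almost by construction. The article does not support that. The rise needs a monitored week in which PAAC is delivered, a unit that registers as extra MVPA, and incomplete compensation outside school. Teachers only log the weekly number of PAAC lessons, so delivery may vary, and one scenario above gives a net fall.

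The other side also argues that Table 1 is a sample-size table, that minutes per day is merely a unit, and that splitting accelerometer data is detail for the full protocol or SAP. This stands in part. The article nowhere says that the data will be analysed only as whole-day totals, and cut-points and wear-time rules do belong elsewhere. But the Statistical Protocol takes its variables from Table 1, and the 60-minute MVPA benchmark there is a whole-day quantity. The article names one quantity in its question and lists another as the outcome, which is more than an omitted detail.

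Three further points stand in full. Whole-day MVPA is a legitimate outcome, since total activity net of compensation matters for health. The SD, the shares and the leisure-time fall are assumptions, and the Z-score footnote leaves open whether 126 refers to a difference in mean minutes. Finally, leisure-time activity is one part of one of three research questions, and nothing shows that the authors would report a whole-day difference as a leisure-time effect.

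**Conclusion.** The point holds as a mismatch between question and listed outcome. In a PAAC school week, the per-day totals mix the delivered unit with any leisure-time response. The delivered part is up to 32 min/day, 16 at half share and 8 at a quarter. It can therefore produce a between-arm difference when leisure-time activity is unchanged or lower, and so the totals do not by themselves answer that part of research question 1. The minutes rest on five delivered units in the monitored week and on the assumed shares; the power figures also rest on the assumed SD of 15 to 30 min/day. The mismatch itself needs none of the SD figures. It calls neither the monitoring nor the use of whole-day MVPA for total activity into question.

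**What to change.** Use the school timetables to split each child's time-stamped actigraph record into school hours and out-of-school time. Then:

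- For the leisure-time question, make the outcome the intervention-minus-control difference in change of out-of-school MVPA (after school plus weekend days, mean min/day).
- Report school-hours MVPA separately, as evidence that PAAC was delivered.
- Keep whole-day MVPA, labelled as total activity, and state that it includes the PAAC unit.

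The cost is obtaining the timetables and a little more analysis work, provided the time-stamped records are kept. The children need no additional measurement.
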